## Methods

### Design

The proposed study is a cluster randomized controlled trial to evaluate the effect of a school-based intervention in nutritional education and physical activity over two school years in children aged between 6 and 10 years, attending primary public schools. Three modes of intervention will be implemented and the results will be measured alongside those of a control group. The intervention modes consist of the following:Intervention 1: Healthy Kiosk and nutritional education (KSEAN);Intervention 2: Optimized physical activity (AFSO), where the physical education classes will be taken by a specialized physical education teacher or a primary teacher with a specialization in physical education. The effective class time will be a minimum of 70 min, during which half of the time should involve undertaking activities of moderate to vigorous intensity;Intervention 3: Healthy kiosk and nutritional education (KSEAN) + Optimized physical activity (AFSO);Control group: Physical education classes will follow the curriculum as indicated for the subject of physical education and health (AFS).

The study will be conducted in 12 clusters (schools) in three regions of Chile (VIII, VI and Metropolitan), distributed in four schools per region, randomly assigned to KSEAN, AFSO, KSEAN+ AFSO or control.

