##### Determination of sample size

The sample size was determined as that required to obtain a standard size of the effect of 0.2 on the BMI z-score, based on a previous nutritional and physical education intervention study conducted in primary schools to prevent childhood obesity by Kain et al. in order to identify this effect in four clusters per intervention mode, with a power of 0.8, a significance of 5% and an inter-cluster coefficient of variance of 0.00012 [35], 140 children per cluster are required along with a minimum of 11 clusters, giving a total of 1540 children. Given that this study was conducted in three regions and that each intervention mode must be conducted in each region, a total of 12 clusters and 1680 subjects are required. Assuming a participation loss of 10% in 2 years of intervention, the total sample size would be 1848 children.

It is anticipated that the grip strength dependent variable will be improved by 20% compared to the study conducted by Rojas C et al. [36]. With the sample size calculated in this manner, in order to have a power of 0.8 at a 95% confidence level, 130 subjects per cluster are required, thereby reaching a total of 1560 children between year 1 and year 4.

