### Data analysis

The data will be validated by the minimum and maximum values. All the statistical analysis will consider the cluster design, in an intention of treating analysis. Additionally, each intervention protocol will be analysed separately to determine the effectiveness of each intervention.

The normality of the data will be assessed by determining the goodness of fit using the Shapiro-Wilk test, while the homogeneity of the variance will be assessed by using the Bartlett and Levene tests. The results from the Shapiro-Wilk test will be used to describe each variable depending on their normality, variables that are normally distributed will be described by the mean ± SD and range of the 95% CI, while variables that do not follow a normal distribution will be described by their percentile distribution. The results will be shown with their respective 95% confidence intervals.

The difference between each group (intervention mode) will be assessed by conducting parametric tests for normally distributed continuous variables (student *t*-test and ANOVA), and non-parametric tests (Wilcoxon, Kruskal-Wallis and Friedman tests) for non-normally distributed continuous variables. The Chi-square test will be conducted for categorical variables (non-continuous). Logistic regression models will also be developed to analyse the probability of change in the result variables for each intervention mode, controlling by age and gender of the participants and considering the impact of the secondary variables. To evaluate the difference between modes of intervention for continuous dependent variables, a multilevel regression analysis with mixed effects will be conducted to make adjustments by co-variables, as these models do consider the experimental design.

STATA 12 (Copyright 1984–2009 StataCorp) and SAS 9.1 (Copyright (c) 2002–2003 by SAS Institute Inc., Cary, NC, USA) will be used to conduct all of the statistical tests and analysis.

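### The 0.8 power is a large-sample figure that makes no allowance for having only 12 schools: on school-level degrees of freedom it is about 67–71% at the plan's ICC, and the mixed model's reference distribution should be fixed in case the true ICC is larger

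*Protocol article*

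**What the plan says.** The Design section of the protocol article states: "The study will be conducted in 12 clusters (schools) in three regions of Chile". They are "distributed in four schools per region, randomly assigned to KSEAN, AFSO, KSEAN+ AFSO or control". That is one school per arm in each region, so three schools per arm.

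The sample-size section aims to "obtain a standard size of the effect of 0.2 on the BMI z-score", "with a power of 0.8, a significance of 5% and an inter-cluster coefficient of variance of 0.00012". It concludes that "140 children per cluster are required along with a minimum of 11 clusters, giving a total of 1540 children", and then raises this to 12 schools and 1680 children so that each mode is present in each region.

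The Data analysis section says that all analyses will take account of the cluster design. For continuous outcomes it adds that "a multilevel regression analysis with mixed effects will be conducted to make adjustments by co-variables, as these models do consider the experimental design". It names no estimation method (REML or ML), no reference distribution and no degrees-of-freedom method.

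**The concern.** Schools are the randomised units, and the between-school variance has to be estimated from 12 of them. With four arms this leaves 12 − 4 = 8 degrees of freedom, or 6 once the two region contrasts are also fitted. Two consequences need checking.

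- **Power.** A sample size built on normal quantiles treats the variance of a school mean as known. If the stated power was obtained that way, it is too favourable for a test whose error term comes from so few schools.
- **Type I error.** A random school effect places the clustering in the model, but with three schools per arm the reference distribution decides whether the 5% level holds. If z tests are used and schools differ more than the near-zero planning ICC implies, some school differences would be reported as intervention effects on BMI z-score, body fat or fitness.

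**Working it through.** **Inputs.** From the sample-size section: effect 0.2 SD, power 0.8, significance 5% (taken as two-sided), ICC 0.00012, 140 children per school. From the Design section: 3 schools per arm, 4 arms, 3 regions. The larger ICCs below (0.002, 0.01, 0.02) are assumptions; the document gives no ICC except 0.00012.

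**1. The plan's own figure**

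- Per arm without clustering: 2 × (1.960 + 0.842)² / 0.2² ≈ 393.
- Design effect: 1 + 139 × 0.00012 = 1.0167.
- Per arm with clustering: 393 × 1.0167 ≈ 399.6, which is 399.6 / 140 = 2.85 schools per arm, or 11.4 schools in four arms.
- Normal-theory power: 0.786 with 11 schools of 140 and 0.820 with 12.

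The stated 11 clusters and 0.8 power are therefore a two-sided normal-quantile calculation. A one-sided version would give 9.0 schools.

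**2. The same inputs with school-level degrees of freedom**

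Noncentrality for one mode against control: 0.2 × √(3 × 140 / (2 × 1.01668)) = 0.2 × √(210 / 1.01668) = 2.874.

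| Reference | Critical value | Power for 0.2 SD | Effect for 80% power |
|---|---|---|---|
| Normal | 1.96 | 82.0% | – |
| t, 8 df (no region) | 2.31 | 71.2% | 0.223 SD |
| t, 6 df (region fitted) | 2.45 | 67.1% | 0.234 SD |

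**3. Type I error of an uncorrected Wald z test from the mixed model**

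With total variance 1, a school mean of 140 children has variance V = ICC + (1 − ICC)/140, and a contrast of two arms has variance 2V/3. In a balanced random-intercept model, V is estimated by the between-school sum of squares divided by 8 or 6 (REML) or by 12 (ML). The school variance is held at zero or above. Null trials were simulated and compared with 1.96. Ranges cover 8 and 6 df. The last column repeats step 2 with the design effect for that ICC.

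| ICC | REML, z | ML, z | Power for 0.2 SD, t on 6–8 df |
|---|---|---|---|
| 0.00012 (plan) | about 4% | about 5% | 67–71% |
| 0.002 (assumed) | 5.4–5.5% | 7–8% | 57–61% |
| 0.01 (assumed) | 8.0–8.5% | 13–16% | 35–38% |
| 0.02 (assumed) | 8.4–9.3% | 14–19% | 24–26% |

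As an example of the last column, at ICC 0.01 the design effect is 1 + 139 × 0.01 = 2.39 and the noncentrality is 0.2 × √(210 / 2.39) = 1.875.

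At the plan's ICC the z test is not inflated, because the school variance is estimated as zero in about 55% of REML fits. There the fitted z test has power of about 76–77% (REML) or 81–82% (ML).

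**The case against.** The strongest reply has four parts.

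- **The plan does not commit to large-sample tests.** Estimation method and degrees of freedom are commonly left to the SAP, which is not shown, and an article condenses further. This stands: the silence is not itself an error, and the statement that mixed models respect the design is not false. It does not rescue the power figure, which is stated and has a large-sample basis.
- **At the plan's own ICC, uncorrected z tests work.** They hold 5% and have 76–82% power. This also stands, but only if the ICC really is close to zero. The value was set for BMI z-score alone, while the model serves all continuous outcomes, including body fat, jump and grip strength, for which no ICC is given.
- **Covariate adjustment and repeated measurements could change the power.** True. The 67–71% refers to an unadjusted comparison at one time point, as does the plan's 0.8.
- **The 6 df presume that region is fitted.** The document does not say so, which is why both 6 and 8 df are shown.

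A reader might infer that the planned analysis rejects a true null 8–19% of the time and also has 67–71% power. The document does not support that. The two figures belong to different ICCs: inflation on that scale needs an assumed 0.01–0.02 and an uncorrected test that the plan never names, and the 67–71% holds only at 0.00012.

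**Conclusion.** The concern holds in two separate parts.

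**Power.** The stated 0.8 makes no allowance for only 12 randomised schools. On the plan's own inputs, power is about 71% (8 df) or 67% (6 df) for a school-level t test, which is 11 to 15 points below the normal-theory 82% at 1680 children. This rests on a two-sided 5% test, equal school sizes of 140 and the stated ICC.

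**Type I error.** This part is conditional. There is no inflation at ICC 0.00012. At 0.002, uncorrected tests would reject about 5% (REML) or 7–8% (ML) of the time; at 0.01–0.02, about 8–9% or 13–19%. The document does not show that such an ICC applies or that z tests will be used. The case for fixing the method is protection if the near-zero planning value proves too low, in which case power would be well below 0.8 as well.

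**What to change.** 1. State that continuous-outcome contrasts between modes use REML with small-sample degrees of freedom (Kenward-Roger or Satterthwaite), or a school-level analysis with region using t on 6 df (8 df without region). Say which degrees of freedom apply when the school variance is estimated as zero, because Satterthwaite-type values need not then equal 6 or 8.
2. Restate the power in the sample-size section on that basis, with its ICC condition: about 67–71% for 0.2 SD at ICC 0.00012, or 80% for about 0.22–0.23 SD. Show how it falls at larger ICCs.
3. In the same edit, reconcile "in order to identify this effect in four clusters per intervention mode" with the three schools per arm that the Design section gives.
4. Do not rely on a permutation test for a single pairwise contrast. Three region pairs give 2³ = 8 arrangements, so the smallest two-sided p-value is 2/8 = 0.25.

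The change needs one option in the analysis code, a sentence in the SAP and a revised power statement. The downside is wider intervals and a less favourable stated power.

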## Conclusion

In relation to the increase in childhood obesity in Chile, there is consensus among researchers, educators and health and education personnel that schools are a favourable environment for actions to prevent and/or control childhood obesity.

Despite the apparent advantages of dealing with obesity in schools, a lack of evidence on the effectiveness of interventions to date has led some to question the wisdom of allocating resources to programmes.

Clearly further studies are required to provide more information on these aspects, and to achieve this, political authorities require specific information on what food and nutrition strategies to prioritize, which, along with physical activity, will provide encouraging results for the control and/or reduction of childhood obesity.

## Abbreviations

AFO: Optimized physical activity
FOSIS: Fund for Solidarity and Social Investment
IC: Confidence interval
ICC: Intracluster correlation coefficient
INTA: Institute of Nutrition and Food Technology
IVE: School Vulnerability Index
JUNAEB: National Board of Student Aid and Scholarships
KSEAN: Healthy food kiosk and nutritional education
MINSAL: Ministry of Health
RSE: Corporate Social Responsibility
SD: Standard Deviation
UTP: Pedagogical Technical Unit
